### Participant eligibility

The study subjects are children with CP aged 6 to 78 months. Because the Paediatric Evaluation of Disability Inventory (PEDI) assessment module is suitable for children under the age of seven, we defined the upper age criterion considering the one-year follow-up period. Children who have had orthopaedic surgery due to CP; children who have congenital muscular disease, hereditary disease, or progressive central nervous system diseases; and children who suffer from severe diseases (i.e., cancer, severe heart disease, or severe infectious disease) are excluded from this study.

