### Treatment

The participants undergo rehabilitation according to their doctors’ clinical care, but they do not receive any intentional treatments. During the period, they can freely start, cease or change any conventional treatments or TKM treatments. The conventional treatments can include PT, OT, ST and other conventional therapy, and the TKM treatments include herbal medicine, chuna, moxibustion and any type of acupuncture, e.g., body acupuncture, scalp acupuncture and pharmacopuncture. The most frequent set of TKM treatments implemented for CP children in South Korea is acupuncture and/or herbal medicine.

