### Rationale for sample size

The sample size was determined on the basis of the primary outcome measure, GMFM-66. Using a 2-sided test, a sample size of approximately 37 children per treatment would assure 80 % power to detect a difference of at least 1.6 points (α = 0.05) assuming a standard deviation of 2.2 and dropout rate of 0.2. This mean change of 1.6 points in GMFM-66 scores was considered a clinically meaningful change in previous studies [17, 19]. We also planned the sub-group analyses considering disease severity measured by GMFCS (2 sub-groups, I-III and IV-V) and age (2 sub-groups, <3 and ≥3) heterogeneity. Therefore, a total of 300 participants will be required.

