**Fig. 2 Fig2:**
[figure not shown]
Process and time line of the observational study. CT, conventional treatment; TKM, traditional Korean medicine; ATx, acupuncture; Mx, medication

For the analysis of effectiveness, multiple variables, including age, severity of illness (indicated by the GMFCS), and treatments, will be converted to propensity scores by logistic regression, and the two groups will be compared by matching or stratification. We expect that using propensity scores will enhance the control variables of heterogeneous conditions. The last observation carried forward method will be used to handle missing data. The change from baseline of the GMFM-66 and PEDI scores at weeks 26 and 52 will be representative outcomes to evaluate effectiveness. These outcomes will be analysed by a two-sample *t*-test for the cross-sectional dataset and by a linear mixed model for the longitudinal dataset [20].

For sub-group analysis, we will analyse the correlation between rehabilitation intensity and functional changes in each group. We will also examine the different outcomes between acupuncture and acupuncture plus herbal medication cases in the TKM combination treatment group.

The number of participants with SAEs and non-SAEs will be reported via analysis of frequency, and the detailed progress of SAEs and related health problems will be disclosed as safety issues. In the case of long-term medication, we will carefully investigate adverse drug reactions using the drug-induced liver injury causality assessment scale [21].

The effectiveness of TKM reported by guardians will be used for further patient-centred outcome research. In the case of participants ceasing TKM treatments, we will investigate the reasons to enhance the feasibility of developing an RCT protocol.

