## Discussion

A previous study reported that there is an increasing demand for CAM, especially traditional Korean medicine (TKM), among Korean children with CP [22]. TKM, which is derived from TCM, is very different from TCM in practice and is widely used in Korea. Only a few clinical case reports have evaluated the effectiveness and safety of TKM; therefore, more data are required to provide optimal information to children with CP and their guardians.

In general in South Korea, children with cerebral palsy concurrently receive their treatments in many rehabilitation clinics and rehabilitation centres in hospitals. Although they often change medical institutions for rehabilitation therapies, conventional therapies usually last approximately 30 min per session. Therefore, if we collect information regarding the types of interventions, the number of medical institutions, and the number of sessions, we can calculate the amount or intensity of intervention to a certain degree for statistical analysis.

The aim of this study is to analyse the effectiveness, safety, and cost-effectiveness of both conventional and TKM combination treatment for children with CP. This study is designed to evaluate the effectiveness of many types of interventions, including TKM, on cerebral palsy and to compare effectiveness between groups with or without TKM. From this initiative, we will attempt to identify the gross effectiveness of interventions, and then we will try to measure the amounts of interventions that can increase outcomes by digitizing intensity, duration, and frequency. We hypothesize that TKM combination treatment for children with CP will have benefits compared with conventional therapy alone, and as such, TKM combination treatment might be promoted in the development of an advanced guideline for integrative rehabilitation. Moreover, the findings of this study might provide informative data for conducting economic evaluations and developing a future randomized controlled trial (RCT) of combination treatment for CP in South Korea.

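### The rehabilitation-intensity question is planned as a within-group correlation with no stated adjustment, so age and GMFCS severity may confound it in either direction

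*Protocol article*

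**What the plan says.** Under Statistical and analytical plans, the sub-group paragraph states that "we will analyse the correlation between rehabilitation intensity and functional changes in each group". It names no covariates.

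The Discussion gives the purpose: "we will try to measure the amounts of interventions that can increase outcomes by digitizing intensity, duration, and frequency". Intensity is to be built from the types of intervention, the number of institutions and the number of sessions, from which "we can calculate the amount or intensity of intervention to a certain degree for statistical analysis".

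The Treatment section makes clear that participants' therapy is not fixed by the study: "they can freely start, cease or change any conventional treatments or TKM treatments".

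Control of confounding is described once, in the effectiveness paragraph of Statistical and analytical plans: "multiple variables, including age, severity of illness (indicated by the GMFCS), and treatments, will be converted to propensity scores by logistic regression", after which "the two groups will be compared by matching or stratification".

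Rationale for sample size names age and severity as sources of heterogeneity: "We also planned the sub-group analyses considering disease severity measured by GMFCS (2 sub-groups, I-III and IV-V) and age" (split at 3 years). Participant eligibility shows how wide the age range is: "The study subjects are children with CP aged 6 to 78 months".

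**The concern.** A correlation between a self-selected exposure and an outcome answers a question about amounts that can increase outcomes only if children with high and low intensity are otherwise comparable. Nothing in the design makes them so. Younger or more severely affected children may receive more therapy, or less, and may also gain motor function at a different rate. If both hold, intensity and change are associated even when therapy amount has no effect, and a real effect can equally be hidden.

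The one adjustment described does not reach this analysis. A propensity score for CT versus CT + TKM balances covariates between those two groups. It says nothing about the balance between a child with many sessions and a child with few inside the same group. That treatments are among its inputs does not change this, because the quantity modelled is still group membership. The linear mixed model is named for the change-from-baseline outcomes, not for the intensity question.

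At stake is a secondary result. A misleading dose association could be carried into later work on therapy amount, because the Discussion expects the study's findings as a whole to help in developing a future randomised trial.

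**Working it through.** **The plan's own figures.** The article gives no figure for the intensity correlation. Its sample size reproduces and supplies the group size used below.

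- Inputs from Rationale for sample size: difference 1.6, SD 2.2, two-sided α 0.05, power 80%, dropout 0.2, total 300.
- n per treatment = 2 × (1.960 + 0.842)² × (2.2/1.6)² = 29.68; divided by 0.8, this is 37.1, matching the stated 37.
- Two treatments × four cells (two GMFCS classes × two age classes) × 37 = 296, close to 300.
- Group size for the illustration: 300/2 × 0.8 = 120. This assumes an equal split and 20% dropout. Groups are formed only at analysis, so the actual split is unknown.

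**One confounder, no dose effect.** Let a confounder have correlation a with intensity and b with functional change, and let intensity have no effect. With linear relations, the expected unadjusted correlation is r = a × b. The chance that it is significant follows from the Fisher transformation:

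P = Φ(√(n−3) × atanh r − 1.96) + Φ(−√(n−3) × atanh r − 1.96), with √(120−3) = 10.817.

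| a = b (assumed) | r | √117 × atanh r | P(significant) |
|---|---|---|---|
| 0.3 | 0.09 | 0.976 | 16% |
| 0.4 | 0.16 | 1.746 | 42% |
| 0.5 | 0.25 | 2.763 | 79% |

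**Two confounders, same direction.** Age and severity were simulated as independent standard normal variables, each correlated a with intensity and a with change. The true dose effect was zero, n = 120, with 4000 replicates. The third results column adjusts for age and severity each split in two and crossed, which mimics working within the planned sub-groups. The simulation splits at the mean, not at the protocol's cut points.

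| a (assumed) | Mean unadjusted r | Significant, unadjusted | Significant, two-by-two classes | Significant, full adjustment |
|---|---|---|---|---|
| 0 | 0.00 | 5% | 6% | 5% |
| 0.2 | 0.08 | 14% | 6% | 5% |
| 0.3 | 0.18 | 51% | 12% | 6% |
| 0.4 | 0.32 | 95% | 35% | 4% |

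At n = 150 per group (no dropout), the unadjusted rates for a = 0.2, 0.3 and 0.4 are 17%, 61% and 98%. Full adjustment stays near 5%.

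**Opposite directions.** If the product of correlations is −0.09 for severity and +0.09 for age, the expected correlation is zero, and the simulated false-positive rate at n = 120 is about 5%. The bias can therefore cancel. By the same arithmetic, a net negative product can offset and mask a true positive dose effect.

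**The case against.** The strongest objection is that the article does not call the correlation raw, bivariate or unadjusted. A reader might infer that an unadjusted analysis has been fixed. The text does not support that: it leaves adjustment unstated, and a fuller document not shown here could supply covariates. What stands is that the article does choose a method, a correlation within each group, and the only confounder control it describes is directed at a different contrast.

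Second, the sentence opens the sub-group paragraph, and the sub-groups in Rationale for sample size are defined by age and GMFCS. Running the correlation within them is a fair reading, though not an explicit one. It would cut the bias considerably (51% to 12%, or 95% to 35%, in the simulation) but would leave residual confounding within broad classes.

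Third, a reader might infer that confounding is established. It is not. The documents give neither its size nor its direction, and opposing effects may cancel. The support is indirect: therapy is freely chosen, and the protocol treats age and severity as needing control elsewhere.

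Fourth, a reader might infer that this analysis is meant to set guidelines on therapy amount. The Discussion does not say so. Its guideline remark concerns TKM combination treatment, and the future trial is to draw on the study's findings in general. The wording about amounts is also tentative, appears only in the Discussion, and is not among the stated aims or outcomes. Correlation is itself an associational term.

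None of this removes the mismatch between the method named and the question about amounts, but it limits the point's weight.

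**Conclusion.** The point holds in a limited form. As written, the within-group correlation has no stated protection against confounding by age and severity, and the propensity score cannot provide it. The result may therefore mislead in either direction about the amounts that can increase outcomes.

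The 42% false-positive rate is an illustration. It rests on no true dose effect, a single confounder correlated 0.4 with both variables, linear relations and 120 children per group. Weaker or opposing confounding gives less, and two confounders acting together give more. None of these strengths comes from the documents.

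This is an inexpensive improvement to a secondary, exploratory analysis. It does not touch the comparison of CT with CT + TKM on the primary outcomes, nor the sample size.

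**What to change.** Replace the correlation with a regression, or extend the planned linear mixed model, with change in GMFM-66 and in PEDI as outcomes and intensity over the same interval as the exposure. Adjust for age, GMFCS level and baseline score, and include a group-by-intensity term so that the slopes in the two groups can be compared. Report the adjusted slope with its confidence interval and label it associational. If a correlation is kept, call it descriptive and say that it does not identify an effect of therapy amount.

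Show results with and without the baseline score. In non-randomised data, measurement error in the baseline can itself affect the slope, so the reader should see whether the conclusion depends on that choice.

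The cost is analysis wording and one extra set of results. Table 1 already schedules demographics at screening, GMFCS, GMFM-66 and PEDI at baseline and months 6 and 12, and treatment surveys every month. Adjustment will not remove confounding by factors that are unmeasured or poorly measured, which is why the associational label is needed.

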**Methods/Design:**

Three hundred children with cerebral palsy aged 6 to 78 months will be recruited from six institutions. Data from each child are collected every month for a one-year period, during which time treatment might be changed or discontinued. A qualified investigator visits the sites to measure effectiveness variables, including Gross Motor Function Measure and Paediatric Evaluation of Disability Inventory. Adverse events and cost-effectiveness variables are collected using surveys conducted at baseline, mid-study, and end of study, as well as monthly tracking surveys. In the analyses, participants will be classified into two groups: group A children will be the conventional treatment group with physical, occupational, speech-language or other conventional rehabilitation therapies, whereas group B children will be the combination treatment group with traditional Korean medicine interventions, that is, herbal medicine, chuna, moxibustion and acupuncture, in addition to conventional treatment.

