### Data collection

Data are obtained by participant survey and investigator measurement at baseline and at specified follow-up times (Table 1).

**Table 1 Tab1:** Schedule of observations

	Screening	Registration	Observation period											
Study month (month)		baseline	1	2	3	4	5	6	7	8	9	10	11	12
Visit number	−1	1						2						3
Visit windows (week)							26 ± 1						52 ± 1	
Informed consent	●													
Demographics	●													
Medical history	●													
Inclusion/exclusion criteria	●													
Height		●						●						●
Weight		●						●						●
Concomitant disorders		●						●						●
Health problems		●						●						●
Survey														
Medication		●	●	●	●	●	●	●	●	●	●	●	●	●
Conventional treatment		●	●	●	●	●	●	●	●	●	●	●	●	●
TKM treatment		●	●	●	●	●	●	●	●	●	●	●	●	●
Health supplements		●	●	●	●	●	●	●	●	●	●	●	●	●
Medical care cost		●	●	●	●	●	●	●	●	●	●	●	●	●
Quality of life		●	●	●	●	●	●	●	●	●	●	●	●	●
Adverse events		●		●	●	●	●	●	●	●	●	●	●	●
Assessment														
GMFCS		●						●						●
GMFM-66		●						●						●
PEDI		●						●						●

●: assessment and observation will be performed

*TKM* traditional Korean medicine, *GMFCS* Gross Motor Function Classification System, *GMFM-66* Gross Motor Function Measure-66, *PEDI* Paediatric Evaluation of Disability Inventory

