#### Participant survey

Parents or guardians respond to survey questionnaires. Data are collected using surveys conducted at baseline, mid-study, and end of study, and monthly tracking surveys will also be used. A baseline interview survey consists of basic characteristics, cause of CP, concomitant disorders, health problems, surgical history, medication, rehabilitation therapies, TKM treatment, health supplements, and medical care cost. An interview survey conducted on the 26th and 52nd weeks will include questions on concomitant disorders and health problems. The monthly tracking survey obtains information on health problems, changes in rehabilitation and treatments, medical care cost, and quality of life (QOL) with the Peds-QL CP module (ver 3.0) [10]. These guardian-reporting documents are collected and managed by the Clinical Research Center of Pusan Korean Medicine Hospital each month for a year. After the parents or guardians complete the forms, the investigators ensure that there are no blank spaces. In the case of insufficient data, we will check the accuracy of the information by reviewing medical records.

We will translate the PedsQL CP module (ver 3.0) into a Korean version and perform concurrent validation and reliability studies.

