### Statistical and analytical plans

The study will present both descriptive and comparative results of conventional treatment and TKM combination treatment. In this study, we define operationally the conventional treatment (CT) group as children who have received only PT, OT, ST, and other conventional therapies, whereas the TKM combination treatment (CT + TKM) group is defined as children who have received at least twelve sessions of any type of acupuncture or 30 days of herbal medication within a 6-month follow-up period in addition to conventional therapies. At the time of analysis, participants will be classified in the conventional or TKM combination treatment group based on the six-month or one-year follow-up information (Fig. 2).

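### A safety comparison by the two treatment groups would leave out children who stopped TKM early, and Table 1 schedules no adverse-event collection at month 1

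*Protocol article*

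**What the plan says.** **Safety outcome.** Under Secondary outcome measurement, the Protocol article counts participants with serious and non-serious adverse events over the study period. Statistical and analytical plans adds: "The number of participants with SAEs and non-SAEs will be reported via analysis of frequency". Neither place names a grouping or denominator.

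**Groups.** The abstract (Methods/Design) puts participants into two groups for the analyses and does not limit this to effectiveness. Statistical and analytical plans defines the conventional group as "children who have received only PT, OT, ST, and other conventional therapies". The combination group must have had "at least twelve sessions of any type of acupuncture or 30 days of herbal medication within a 6-month follow-up period", on top of conventional therapy. It then says that "participants will be classified in the conventional or TKM combination treatment group based on the six-month or one-year follow-up information". Under Treatment, families are told that "they can freely start, cease or change any conventional treatments or TKM treatments".

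**Collection of adverse events.** The abstract states: "Adverse events and cost-effectiveness variables are collected using surveys conducted at baseline, mid-study, and end of study, as well as monthly tracking surveys". The Participant survey section describes the monthly form differently: "The monthly tracking survey obtains information on health problems, changes in rehabilitation and treatments, medical care cost, and quality of life". Adverse events are not in that list. In Table 1 (Data collection), the row "Adverse events" is marked at baseline and at months 2 to 12, and is blank at month 1.

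**The concern.** Safety is one of the three stated aims, and the question asked is how safe combination treatment is. A group that a child enters only after a minimum amount of TKM excludes those who tried it and gave up. A reaction is one reason for giving up, so the excluded children may carry more harm than those who stayed. If safety is then compared between the two defined groups, the combination group may look safer than TKM is among all who started it.

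The blank at month 1 is a separate matter. It is the first follow-up contact after registration. A site working from Table 1 would not ask about adverse events there, while a site working from the abstract would.

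**Working it through.** The plan gives no adverse-event or early-stopping figure, so there is nothing of its own to reproduce. The check has three parts.

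**1. Do the two definitions cover every enrolled child?**

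- No TKM at all: conventional group.
- At least 12 acupuncture sessions, or 30 days of herbal medication, within a 6-month period, plus conventional therapy: combination group.
- Some TKM but below both thresholds, for example three sessions or ten herbal days: not conventional only, and not combination. No group.
- Only chuna or moxibustion: both count as TKM in the abstract and under Treatment, but neither enters the threshold. No group.

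So the definitions are not exhaustive, although the text classifies participants into one group or the other.

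**2. What would a by-group safety table lose?** All inputs here are assumptions, because the article supplies none. Let N = 150 children start TKM (half of the planned 300), p = 10% be the event risk in those who reach the threshold, s the share who stop below it (5–20%), and q the event risk in those who stop (10–50%).

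- Rate shown for the combination group: p = 10%.
- Rate among all starters: (1 − s)p + sq.
- Affected children left out: N·s·q.
- Share of affected children left out: sq / [(1 − s)p + sq].

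| s | q | All starters | Affected, left out | Affected, total | Share left out |
|---|---|---|---|---|---|
| 5% | 10% | 10% | 0.75 | 15 | 5% |
| 10% | 30% | 12% | 4.5 | 18 | 25% |
| 20% | 50% | 18% | 15 | 27 | 56% |

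For the last row: 150 × 0.20 × 0.50 = 15; 150 × 0.80 × 0.10 = 12; 15 + 12 = 27; 27/150 = 18%; 15/27 = 56%.

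The rate is understated only when q exceeds p. When q equals p (first row), affected children are left out but the rate is unchanged. In a pooled count over all enrolled children, the grouping rule leaves out nobody.

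**3. When are adverse events collected?**

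- Abstract: baseline, mid-study, end of study, and monthly.
- Table 1: 12 marks, at baseline and months 2–12. The other monthly survey rows have 13, at baseline and months 1–12. The adverse-event row has as many cells as the header, so the blank is not a shifted column. Month 1 is the only unmarked follow-up month.
- Participant survey section: adverse events not named. Health problems are named as monthly, but Table 1 marks them only at baseline, month 6 and month 12. By the table, then, neither item is scheduled at month 1.

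**The case against.** A reader might infer that the safety count itself misses early harm. The documents do not support that. Neither statement of the safety outcome restricts it to the two groups, and the explicit group comparison by propensity score is set out for effectiveness. A count over all participants keeps every early stopper. This part of the objection stands, and it confines the point to a comparison by group. Such a comparison is likely but not stated for safety: the abstract's two-group rule is general, the Study design section lists adverse events among what will be analysed and then calls the study a comparison of the two groups, and the analysis section promises comparative results.

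A reader might also infer a decision not to ask about harm in the first month. One blank cell set against the abstract's monthly collection is an inconsistency and may be a slip. The month-2 form might look back over month 1, but no recall period is given. Nor is month 1 of the study necessarily a child's first month of TKM: TKM use is already recorded at baseline, four of the six sites are TKM institutions (one hospital and three clinics), and no new-user criterion is stated.

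Some text helps. Reasons for ceasing TKM will be investigated, and the course of serious events will be disclosed. But the first is for the feasibility of a later randomised trial, and neither gives early stoppers a place in a group comparison. The liver-injury assessment is stated for long-term medication.

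Finally, a safety population and rates per unit of exposure time are commonly left to an analysis plan, and their absence is not held against this article. What remains is a stated pair of definitions that does not cover the children enrolled. Fig. 2, cited for the classification, is not shown in the text available, so whether it places sub-threshold children somewhere cannot be judged.

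**Conclusion.** The point holds in a limited form. Children with sub-threshold TKM, or with only chuna or moxibustion, belong to neither defined group. A safety comparison by these groups would leave them out and could understate harm, if those who stop early have more events than those who continue. The size is unknown. The 10% against 10–18% above, with about 1 to 15 affected children (5–56%) left out, shows what assumed inputs would give and is not an estimate for this study. A figure such as 5% against 0%, got by counting only events that made a child stop below the threshold, would be circular: those events are absent above it by construction.

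Separately, Table 1 conflicts with the abstract on month 1, and the monthly survey contents do not name adverse events. That contradiction rests on no assumption. Both matters should be corrected, and both are cheap to correct.

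**What to change.** - **Safety grouping.** In Statistical and analytical plans, state that safety is compared by any TKM exposure (at least one session or dose of any TKM modality, including chuna and moxibustion) versus none. Keep the 12-session or 30-day groups for effectiveness.
- **Schedule.** Mark adverse events at month 1 in Table 1, and name them among the contents of the monthly tracking survey in the Participant survey section, so that both agree with the abstract.

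The cost is one item on a form that guardians already complete at month 1, and one extra tabulation. No visit is added and treatment does not change.

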## Methods/Design

### Study design

The study team is conducting a one-year, multi-site, prospective observational study of rehabilitation for children with CP. We are recruiting the children at two university-affiliated hospitals, one TKM hospital and three TKM clinics. The children with CP receive treatments from doctors and therapists in each clinic or centre, and one independent investigator assesses functional changes in participants and collects survey documents from their guardians or parents. We will analyse changes in the children’s functional development and health condition, the number of adverse events, and monetary resources spent for rehabilitation during this period. This design is a comparative observational study of a conventional treatment group and a TKM combination treatment group (Fig. 1).

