### Secondary outcome measurement

The secondary outcomes involve safety and cost-effectiveness (utility) analysis components. One secondary outcome will be the number of participants with serious adverse events (SAEs) and non-SAEs during the study period. Cost data include direct medical and non-medical costs, indirect costs and productivity losses. Utility scores (EQ-5D) will be estimated from the mapping equation of PedsQL developed by Khan et al. [18], and then will be used for calculating quality-adjusted life years (QALYs) based on the area under the curve method. Cost-utility analysis will be conducted from a societal perspective, which includes direct medical costs, direct non-medical costs, and indirect non-medical costs measured as productivity loss of parents and other caregivers.

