Medical costs will be analysed for distribution characteristics, and we will perform a descriptive analysis of quantitative data. Each variable will be verified by statistical sensitivity and value analysis. Constant tariff values of the initial QOL measurements will be used to estimate QALYs between each follow-up interval, and a straight line of final QOL measurements will be used for extrapolation. An incremental cost-effectiveness ratio table and a cost-effectiveness plane will provide mean values of parameters, and a probabilistic sensitivity analysis will be conducted using distributions of estimated values of major variables. The analyses will be based on a societal perspective, and the discount rate will be 5 % based on the reference case recommendation of the Panel on Cost-Effectiveness in Health and Medicine and the Guidelines of Economic Evaluation of Medical Supplies in South Korea.

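### The QALY rule is stated in two ways that give different results, and no propensity or baseline-utility adjustment is described for the cost-utility comparison

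*Protocol article*

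**What the plan says.** The protocol article describes the QALY calculation in two places.

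- **Secondary outcome measurement:** utilities mapped from PedsQL "will be used for calculating quality-adjusted life years (QALYs) based on the area under the curve method".
- **Statistical and analytical plans**, economic paragraph: "Constant tariff values of the initial QOL measurements will be used to estimate QALYs between each follow-up interval", after which "a straight line of final QOL measurements will be used for extrapolation".

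Table 1 schedules quality of life at baseline and in each of months 1 to 12. The Participant survey section also places it in the monthly tracking survey.

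On adjustment, the propensity-score plan in Statistical and analytical plans opens with "For the analysis of effectiveness, multiple variables". It then names change in GMFM-66 and PEDI as the outcomes that represent effectiveness. The economic paragraph comes later and says: "An incremental cost-effectiveness ratio table and a cost-effectiveness plane will provide mean values of parameters". A probabilistic sensitivity analysis follows. That paragraph mentions neither matching, nor stratification, nor baseline utility. The study is observational, and children are assigned to a group at analysis according to the treatment they received.

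**The concern.** Two analysts following the two sections could compute different QALYs from the same data. Area under the curve normally means joining successive utilities by straight lines. Holding the first value of each interval constant draws a staircase instead, so each change is credited one interval late, although the value at the end of the interval has been observed.

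The adjustment point may matter more. The primary outcomes are changes from baseline, which already remove part of any difference in starting level. QALYs add up utility levels, so a difference present before follow-up counts in every month. The groups are self-selected, so a starting difference is plausible, yet the adjustment that is described is tied to effectiveness. Cost-effectiveness is one of the study's three aims, and its results are meant to inform later economic evaluations.

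**Working it through.** The document gives no utility or QALY figures, so there is no stated number to reproduce. The sizes below are illustrations under labelled assumptions.

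**Inputs from the document**
- Follow-up: one year (Study design).
- Quality of life: 13 points, baseline and months 1 to 12 (Table 1), so the interval is h = 1/12 year.
- Rule A: area under the curve, taken as trapezoidal (Secondary outcome measurement).
- Rule B: initial value held constant over each interval, with initial read as the start of that interval (Statistical and analytical plans).

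**Inputs assumed**
- D: net utility change over the year, 0.05, 0.10 or 0.20.
- b: baseline utility difference between groups, 0.02 to 0.05.

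**Step 1: general gap.** With utilities u0 to u12:
- Trapezoid: T = sum of h × (u(k−1) + u(k))/2, for k = 1 to 12.
- Constant rule: S = sum of h × u(k−1), for k = 1 to 12.
- S − T = −(h/2) × (u12 − u0) = −(u12 − u0)/24.

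The gap depends only on the net change between first and last value.

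**Step 2: linear change of D.** With u(k) = u0 + D × k/12:
- T − u0 = D/2.
- S − u0 = D × (0 + 1 + … + 11)/144 = 66D/144 = 11D/24.
- Ratio = (11/24)/(1/2) = 11/12 = 0.917, so the constant rule is 8.3% low.
- ICER factor at the same incremental cost = 12/11 = 1.09. Here D is the between-group difference in change, with no baseline difference.

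| D (assumed) | Trapezoid | Constant rule | Gap |
|---|---|---|---|
| 0.05 | 0.0250 | 0.0229 | 0.0021 |
| 0.10 | 0.0500 | 0.0458 | 0.0042 |
| 0.20 | 0.1000 | 0.0917 | 0.0083 |

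**Step 3: other shapes.**
- Utility rises and returns to its starting value: u12 − u0 = 0, so there is no gap.
- Utility reaches D by month 1 and stays there: T − u0 = D/24 + 11D/12 = 11.5D/12. The gap is D/24, a proportion of (1/24)/(11.5/12) = 4.3%.

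**Step 4: baseline difference.** If the groups start b apart and run in parallel for the year with no treatment effect, the QALY difference is b × 1 year = b, that is 0.02 to 0.05. A genuine gain rising linearly to 0.05 to 0.10 is worth D/2 = 0.025 to 0.05 QALY. An unadjusted imbalance of the assumed size would therefore be comparable with the effect sought. It is also roughly ten times the interpolation gap for the same gains (0.002 to 0.004).

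**The case against.** **On the QALY rule.** A staircase also has an area under it, and the outcome section never says trapezoidal. The later sentence could simply specify how the curve is drawn. This is fair and softens the contradiction. It does not rescue the rule, which still discards an observed value in every interval. It is also true that the numerical effect on monthly data is small.

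**On adjustment.** The article condenses a fuller plan, and means from a matched sample are still means. A reader might infer that the ICER will use raw group means. The text does not say so. What stands is narrower: the only adjustment described is introduced for effectiveness, and none is described for costs or QALYs.

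**Stronger readings that the document does not support**
- *The constant rule understates every QALY change.* Step 3 shows no gap when utility returns to its start. The 8.3% belongs to a linear trend.
- *The ICER could double.* That needs 26-week intervals, where the constant rule would recover only half of a linear gain. Those visits are for GMFM-66 and PEDI; quality of life is scheduled monthly.
- *The mapping cannot work because the survey collects "quality of life (QOL) with the Peds-QL CP module (ver 3.0".* Which scores the equation accepts can be learned only from the cited source, which is not at hand. No error is shown, so an extra parent form or a different base case is not justified on this ground.
- *Extrapolation must go.* The horizon is not stated in the article, but whether to extrapolate is a choice of time horizon, and a 5% discount rate suggests that more than one year may be intended.

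**Conclusion.** The point holds in limited form. The two QALY statements need reconciling, and the constant-value rule is the weaker method for monthly data. Its cost is D/24 QALY for a net change of D: 8.3% of the gain, or about 9% on the ICER, for a linear course, and nothing if utility returns to baseline. These figures assume that area under the curve means trapezoidal and that initial means the start of each interval.

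The absence of any described adjustment for the cost-utility comparison is potentially the larger issue, because a persisting baseline utility difference enters the one-year QALY difference in full. The 0.02 to 0.05 used here is an assumption. Nothing in the document shows that such an imbalance exists, or that the fuller plan leaves it uncorrected. The change is worth making, but neither part undermines the study's primary comparison.

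**What to change.** In Statistical and analytical plans:

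1. Replace the constant-value sentence with trapezoidal area under the curve through the baseline and monthly utilities, so that it agrees with Secondary outcome measurement.
2. State that incremental cost and incremental QALY will be estimated with the same propensity method as effectiveness, with additional adjustment for baseline utility.
3. Bootstrap incremental cost and incremental QALY jointly, resampling children, to populate the cost-effectiveness plane.

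The cost is a few lines of analysis text and some programming. Table 1 already schedules the baseline and monthly quality-of-life scores, so no new form, visit or participant is needed.
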